## Abstract

**Background:**

Palliative care is a medical specialty centered on improving the quality of life (QOL) of patients with complex or life-threatening illnesses. The need for palliative care is increasing and with that the rigorous testing of triage tools that can be used quickly and reliably to identify patients that may benefit from palliative care.

**Methods:**

To that aim, we will conduct a two-armed stepped-wedge cluster randomized trial rolled out to two inpatient hospitals to evaluate whether a machine learning algorithm accurately identifies patients who may benefit from a comprehensive review by a palliative care specialist and decreases time to receiving a palliative care consult in hospital. This is a single-center study which will be conducted from August 2019 to November 2020 at Saint Mary’s Hospital & Methodist Hospital both within Mayo Clinic Rochester in Minnesota. Clusters will be nursing units which will be chosen to be a mix of complex patients from Cardiology, Critical Care, and Oncology and had previously established relationships with palliative medicine. The stepped wedge design will have 12 units allocated to a design matrix of 5 treatment wedges. Each wedge will last 75 days resulting in a study period of 12 months of recruitment unless otherwise specified. Data will be analyzed with Bayesian hierarchical models with credible intervals denoting statistical significance.

**Discussion:**

This intervention offers a pragmatic approach to delivering specialty palliative care to hospital patients in need using machine learning, thereby leading to high value care and improved outcomes. It is not enough for AI to be utilized by simply publishing research showing predictive performance; clinical trials demonstrating better outcomes are critically needed. Furthermore, the deployment of an AI algorithm is a complex process that requires multiple teams with varying skill sets. To evaluate a deployed AI, a pragmatic clinical trial can accommodate the difficulties of clinical practice while retaining scientific rigor.

**Trial registration:**

ClinicalTrials.gov NCT03976297. Registered on 6 June 2019, prior to trial start.

**Supplementary Information:**

The online version contains supplementary material available at 10.1186/s13063-021-05546-5.

## Background

Palliative care is a medical specialty centered on improving the quality of life (QOL) of patients with complex or life-threatening illnesses through the prevention and management of pain and other problems, be it physical, psychosocial, and/or spiritual [1].

As patient populations in western countries are aging and becoming more complex, often requiring care from multiple specialties, there is a growing recognition of the need for specialty palliative care teams to engage with patients earlier in their disease course. A consequence of this increased demand is exemplified by the growing mismatch between clinical care and patient preferences at the end-of-life. For example, research has demonstrated that most people prefer to die at home despite the majority dying outside of the home (nursing home or hospital) [2, 3]. Palliative care specialists excel in goals of care and patient preference discussions. Unfortunately, palliative care expertise is often an underutilized resource, and the current model of care and incentives may relegate palliative care as a “last resort” after all attempts at cure have been exhausted [4]. This delay can lead to suboptimal symptom management for pain, lower quality of life, and even reduced survival [5–8]. In addition to these unrealized benefits, palliative care has been shown to be inversely associated with aggressive medical interventions and emergency room (ER) visits, hospital and intensive care unit (ICU) admission, and death in the last weeks of life, all of which are indicative of low value care [9–11]. Demand for appropriate palliative care will and should increase, and with that, policy initiatives and referral triage tools that lead to timely high-quality palliative care services will need to be implemented [12]. Triage tools can be used quickly and reliably to identify patients that may benefit from palliative care, thereby leading to high value care and improved outcomes.

### Risk scores

The development of risk stratification and triage tools for palliative care services has an extensive history with early methods such as The Palliative Prognostic Score (PaP) [13, 14]. Although a complete enumeration of scores in this space is out of scope, there are three aspects of palliative care scoring that are important to mention. First, many palliative care tools often use proxies for palliative care need. For example, mortality tends to be the most common proxy usually in the form of the surprise question—“Would I be surprised if this patient died in the next 12 months?” Although straightforward, mortality as a proxy is substandard, because many patients who are at risk of mortality do not necessarily need palliative care and many patients can benefit from palliative care interaction, even if their risk of short-term mortality is low. Other scores have modeled proxies such as use of hospice services but still limit care to end of life and not the entire spectrum of palliative care needs [15, 16]. Second, palliative care tools often have a targeted timeframe or specified population. For instance, early palliative care scores were focused on patients with cancer, whether late stage or early stage [17]. Subsequently, scores have been developed specifically for inpatient, either general floor or ICU units or community based [18–20]. Although these scores have greater utility, they limit the ability to transfer to other populations which may limit legitimate palliative care need. Third, the complexity of a score is often an important consideration. Earlier models have utilized scores that were simple and easy to calculate and could be done through clinical examination. Recently with the advent of artificial intelligence (AI) and near universal adoption of electronic medical records (EMR), scores are now being developed that utilizes large and complex types of routinely collected data for predictions. Avati et al. developed a deep learning algorithm on EMR data utilizing a model with 13,654 features predicting mortality, and Jung et al. developed an outpatient mortality prediction algorithm utilizing 1880 features and using gradient boosting machines (GBMs) [20, 21].

### Development of integrated palliative risk score algorithm

Informed by these considerations, a machine learning algorithm trained on EMR data and fully integrated into an IT solution focusing on the identification of patients who may benefit from early palliative care review was developed on inpatients from a large academic medical center. The solution, known as Control Tower, pulls disparate data sources centered on a machine learning algorithm which predicts the need for palliative care in hospital. The algorithm along with other key patient indicators was integrated into a graphical user interface (GUI) which allows a human operator, known as the Control Tower Operator (CTO) to review the algorithm predictions and subsequently record the operator’s assessment.

### Evaluation of AI

Despite the large number of published risk scores in the literature for palliative care needs, to the best of our knowledge, there has been a lack of research assessing wide scale *evaluation and implementation* of palliative risk scores into clinical practice. Often scores are tested based solely on predictive performance with validation consisting of clinical review. As hypothesized by Spiegelhalter, it is not enough for algorithms to be trusted by simply publishing research showing predictive performance (phase I) or clinical assessment (phase II); two additional phases are needed. First, there should be field testing with clinical trials demonstrating an impact on clinical outcomes (phase III) as well as an infrastructure to ensure prospective monitoring during routine use [22]. There have been some encouraging and notable exceptions nonetheless; in Courtright et al., the authors published an EHR algorithm for palliative care with a pre-post evaluation on frequencies of consults, advance care planning (ACP) documentation, home palliative care and hospice referrals, code status changes, and length of stay [23].

### Aims of the study

The objective of this study is to evaluate whether the Control Tower solution accurately identifies patients who may benefit from a comprehensive review by a palliative care specialist and decreases time to receiving a palliative care consult in hospital. By creating an algorithm that automatically screens and monitors patient health status during their hospitalization, the hypothesis being tested is that patients will receive *needed* palliative care earlier than under the usual course of care.

### Trial design

To accomplish the primary aim, we will use a two-armed stepped-wedge cluster randomized trial rolled out to both inpatient hospitals in Mayo Clinic, Rochester. Trial units will receive a computerized assessment of patients in the hospital identified to be at risk of needing palliative care services where control units will receive the usual source of care.

## Methods/design

### Study setting

This is a single-center study which will be conducted from August 2019 to November 2020 at Saint Mary’s Hospital & Methodist Hospital, Mayo Clinic, Rochester, Minnesota. The nursing units chosen for the study have a mix of complex patients from Cardiology, Critical Care, and Oncology and had previously established relationships with palliative medicine.

### Eligibility criteria

The recruitment and enrollment is broad and is designed to mimic the actual use of the Control Tower in practice. To be included in the trial, patients will need to be admitted to either inpatient facility during the study period. Patients will need to have a risk score of at least 7 (out of 100) from the algorithm. Patients will be excluded from review if they under the age of 18, previously seen by palliative care during the current hospital encounter, currently enrolled in hospice, or currently followed by a palliative care team. In addition, patients with an expected discharge in the next 24 h and patients who do not provide research authorization to review their medical records for general research studies in accordance with Minnesota Statute 144.335 will be excluded from the study.

### Intervention

A full description of the Control Tower interface can be learned through Murphee et al. [24]. Briefly, the Control Tower is a workstation and software tool that extracts medical data, processes the prediction algorithm, and presents the results through an ordered patient list. Currently, the algorithm is running on all inpatients in both study hospitals in an automated monitored process. A screenshot of the interface can be seen in Fig. 1. In addition to the algorithmic score, additional data on comorbidities, laboratory values, and hospital events are available and presented to give the score context. Patients receive scores from the Control Tower (0–100; higher scores indicate increased need) for palliative care and are subsequently ranked from highest to lowest need with each score colored into tertiles: red (7 or greater), yellow (less than 7, greater than or equal to 4), and white (less than 4). Patients with previous palliative care in their hospital stay have their scores labeled green.

**Fig. 1 Fig1:**
[figure not shown]
Screenshot of the Control Tower user interface

The intervention will include a CTO who will interact with the inpatient palliative care consult service at both study sites. The CTO will monitor the Control Tower during weekday normal business hours (Monday through Friday; 8 am–5 pm) and select, once a day, a cohort of patients with the highest need who may benefit from palliative care review. The operator will assess for any additional exclusion criteria in developing the final list. After all screening is finished, the CTO will select the top 12 patients to be sent to palliative care in a file through email. The number 12 was agreed upon to match the expected capacity of the palliative care team and to maintain regularity throughout the trial. The file will consist of the patient identifying information, along with the algorithmic score indicating probability of needing palliative care, and contextual factors such as the hospital unit they are in and what factors in the model are driving the score. The palliative care team member who is on service will also assess the need for each patient through the daily report and record whether they agreed with the algorithm’s conclusion or not. For those agreed upon patients who are also in the intervention arm, the palliative care team will approach the attending clinical team to suggest a palliative care referral for the patient.

The utilization of a new tool such as the Control Tower to identify patients appropriate for palliative care can be disruptive to standard clinical workflows and processes. To help ensure proper dissemination of these new referral patterns, we engaged with a communications specialist and worked directly with area practice leaders to set up a communication plan.

Patients who are not in an intervention period will receive the standard of care. The usual source of care for both the intervention group and the control group delivered by the specialty palliative care consultation intervention will remain consistent, with a billable palliative care provider conducting a comprehensive palliative care review (symptom assessment, psychosocial-spiritual assessment, goals of care discussion and recommendations as indicated) along with involvement of an interdisciplinary team (evaluation with specialty palliative care nurses, social worker, chaplain). This is feasible given we can easily control the communication between the palliative care team and the attending teams to prevent any contamination between clusters. We calibrated the prediction model and the Control Tower review to match the average capacity of the palliative care service, knowing that that they will still receive palliative care consults through the traditional pathway of the attending care team consulting Palliative Medicine directly. This additional measure increases the likelihood the control group gets the usual source of care.

### Outcomes

For all study outcomes, data will be collected through either the electronic medical record or administrative billing system at trial completion and unless otherwise noted each outcome will be determined during the patient’s inpatient stay. The primary outcome will be time to palliative care as measured by the electronic record of a consult by Palliative Medicine. Data will go through quality checking quarterly, at each step during the burn-in period, and before finalization.

The secondary outcomes are as follows:
The number of inpatient palliative care consults—measured by the number of palliative care consults in the inpatient units of interest.Time to palliative care per unit—measured as time in hours from alert to the electronic record of consult by the palliative care team in the inpatient setting for each of the 12 nursing units.Transition time to hospice-designated bed—for all patients with Medicare insurance the time from alert until transferred to a hospice-designated bed for an inpatient encounter.Time to hospice designation—measured as time in hours from alert to the electronic record of consult by the hospice care team for an inpatient encounter.Emergency Department visit within 30 days of discharge—measured by the number of study participants who upon discharge from the inpatient setting are readmitted to the Emergency Department at any Mayo Clinic facility within 30 days (excluding inpatient readmissions through the Emergency Department).Hospitalization or readmission within 30 days of discharge—measured by the number of study participants who upon discharge from the inpatient setting are readmitted to an inpatient unit at any Mayo Clinic facility within 30 days (excluding transfers and planned readmits).ICU transfers—measured by the number of study participants who transferred to an ICU during their inpatient stay.Ratio of inpatient hospice death to non-hospice hospital deaths—measured by the number of deaths of study participants in hospice designated beds by the number of deaths in non-hospice beds.Rate of discharge to external hospice—measured by the number of participants whose electronic health record indicates discharge to external hospice.Inpatient length of stay—measured as time from admission to discharge from hospital for all study participants.

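### ICU transfer is counted over the whole stay, so transfers before the alert, which the intervention cannot affect, may dilute its odds ratio towards 1

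*Protocol article*

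**What the plan says.** **Outcome window.** The Outcomes section sets a general rule that "unless otherwise noted each outcome will be determined during the patient’s inpatient stay". It measures ICU transfers by "the number of study participants who transferred to an ICU during their inpatient stay". Nothing limits the count to the time after the alert.

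**Other outcomes in the same list.** Three secondary outcomes start at the alert: time to palliative care per unit, transition to a hospice-designated bed, and time to hospice designation. The last of these is "measured as time in hours from alert to the electronic record of consult by the hospice care team for an inpatient encounter". Length of stay, by contrast, is "measured as time from admission to discharge from hospital for all study participants".

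**When exposure can begin.** Under Eligibility criteria, "Patients will need to have a risk score of at least 7 (out of 100) from the algorithm". Under Intervention, the operator works weekday business hours, has to "select, once a day, a cohort of patients with the highest need who may benefit from palliative care review", and sends on at most 12 names. Palliative care then records agreement or disagreement. Only for agreed patients in the intervention arm does it approach the attending team.

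**Who is in the units.** Study setting states: "The nursing units chosen for the study have a mix of complex patients from Cardiology, Critical Care, and Oncology". The exclusions under Eligibility criteria do not mention patients already in an ICU.

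**Analysis.** The Data analysis plan uses logistic regression with the same design features for binary secondary outcomes. A yes/no record of ICU transfer per participant falls under that rule.

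**The concern.** The intervention can change only what happens after a patient has been flagged. An ICU transfer earlier in the same admission is part of the patient's baseline history, yet the definition counts it as an outcome. Such transfers should be about equally common under control and intervention conditions, so they add the same block of events to both and make the arms look more alike.

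The definition also leaves open what to do with a participant who is already in an ICU when flagged. If the move that brought the patient there counts, that patient is an event whatever the intervention does. If it does not count, the patient sits in the denominator and cannot have an event without first leaving the ICU.

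The Background names ICU admission among the markers of low-value care with which palliative care is inversely associated. A null result on this outcome would therefore be read as substantive, when part of it could come from the counting window.

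**Working it through.** The article states no rate, effect or power for ICU transfer, so there is no figure of its own to reproduce. The check is of direction, with a range of assumed sizes.

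**Inputs**
- From the article: whole-stay window (Outcomes), logistic regression for binary outcomes (Data analysis plan), and 2294 simulated encounters (Data analysis plan), used only for the power comparison below.
- Assumed: post-alert ICU transfer risk of 10% in control (q) and 7% under intervention; share p0 with a pre-alert transfer of 0% to 30%, equal in both arms; the same post-alert risk whether or not there was an earlier transfer.

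**Formula.** Risk as the plan counts it = p0 + (1 − p0) × post-alert risk.

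With p0 = 0, the odds ratio is (0.07/0.93)/(0.10/0.90) = 0.68.

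With p0 = 0.20, control is 0.20 + 0.80 × 0.10 = 0.280 and intervention is 0.20 + 0.80 × 0.07 = 0.256. The odds ratio is (0.256/0.744)/(0.280/0.720) = 0.88.

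| Pre-alert share | Control | Intervention | Difference (points) | Risk ratio | Odds ratio |
|---|---|---|---|---|---|
| 0% | 0.100 | 0.070 | −3.0 | 0.70 | 0.68 |
| 10% | 0.190 | 0.163 | −2.7 | 0.86 | 0.83 |
| 20% | 0.280 | 0.256 | −2.4 | 0.91 | 0.88 |
| 30% | 0.370 | 0.349 | −2.1 | 0.94 | 0.91 |

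A second set of assumptions, 20% against 16%, starts at an odds ratio of 0.76 and gives 0.83, 0.87 and 0.89 at the same three shares.

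**Loss of power, as a comparison only.** Take 2294/2 = 1147 per arm and ignore clustering and period effects. For 10% against 7%, power falls from 73% to 40%, 25% and 18% at shares of 10%, 20% and 30%. These are not the trial's power; they show how the window alone changes it.

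**If patients already in an ICU can never count.** With 20% such patients, the risks are 0.80 × 0.10 = 0.080 and 0.80 × 0.07 = 0.056. The risk ratio stays 0.70 and the odds ratio is (0.056/0.944)/(0.080/0.920) = 0.68. Only the difference shrinks, from −3.0 to −2.4 points. Dilution of the odds ratio therefore depends on pre-alert transfers being counted.

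**Length of stay.** Assume 6.0 against 5.1 post-alert days and 2 pre-alert days in both arms. The totals are 8.0 and 7.1. The difference is still −0.9 day, while the ratio moves from 0.85 to 7.1/8.0 = 0.89. The mean difference is not biased; it only loses precision.

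**The case against.** The whole-stay window is declared as a general rule, and a count needs no time origin in the way a time-to-event outcome does. The differing windows are therefore not a contradiction. That is right, and the point does not rest on inconsistency. It rests on counting events that precede exposure.

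Two stronger readings are tempting. A reader might infer that several clusters are ICUs and that nearly every patient in them has the outcome. The article does not support this. It describes a mix of patients that includes Critical Care, calls the clusters floor units under Participant timeline, and does not say how many, if any, are ICUs. Nor does it say that a direct ICU admission is a transfer.

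A reader might also infer that length of stay has the same fault. It does not. Admission to discharge is the conventional measure of resource use, and its mean difference is unbiased.

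The size may be small. The algorithm runs automatically on all inpatients, so a qualifying score could come early in the stay, with few transfers before it. This stands: no magnitude can be claimed.

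A post-alert definition carries its own risks. Listing depends on operator judgement and a cap of 12, and providers are not blinded, so starting the clock at listing could bring in selection related to arm. Patients in an ICU at the alert can also leave and return, so excluding them outright would discard real post-exposure events. Both points stand and shape the fix.

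Finally, the dilution is conservative in expectation and the outcome is secondary. This limits the consequence but does not make the definition sound.

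**Conclusion.** The concern holds for ICU transfers. As defined, the outcome includes transfers before the alert, which the intervention cannot affect, and these would pull the planned odds ratio towards 1. That some counted transfers precede exposure is an inference from the unit mix and the lack of an ICU exclusion; the article does not state it.

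The size cannot be computed from the article. In the main illustration, 0.68 becomes 0.83 to 0.91 for pre-alert shares of 10% to 30%. This rests on assumed rates, equal pre-alert shares in the two arms, and pre-alert transfers being counted. Chance imbalance in pre-alert transfers could move a single result either way.

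The primary outcome is untouched. Length of stay needs no change.

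**What to change.** Redefine the outcome as an ICU transfer occurring after the first logged score of at least 7 while the patient is eligible on a study unit. Apply this start time identically under control and intervention conditions, and do not tie it to operator listing. For patients in an ICU at that time, either count only a new ICU transfer after they have left it, or analyse them separately, and state which.

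No new data collection should be needed. The algorithm runs on all inpatients, the Data management section says predictions are logged at every call, and outcomes come from the electronic record.

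The cost is fewer counted events. A little dilution also remains, because the arms diverge somewhat after the qualifying score; that is the price of a start time that does not depend on arm. The whole-stay count can be kept as a descriptive figure.

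Leave length of stay as it is. Time from alert to discharge is at most an optional supplementary analysis, which would improve precision and avoid dilution on a ratio scale.
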